### **7.8.2.3 Lactate and procalcitonin measurements**

Lactate and procalcitonin will be measured at patient enrolment (V1), 24 hours after treatment initiation (V3), 48 hours after treatment initiation (V4), and 72 hours (V5) after treatment initiation (see treatment schedule p. 8). Blood samples will be obtained through an arterial, peripheral or central venous line.

### **7.8.2.4 Sampling recommendations**

Sampling, handling and storage details will be described in more detail in a study specific procedure and presented during the study training.

### **7.8.2.5 Sampling details**

Blood samples: No additional puncture of the patient is necessary.

In total ~70 ml blood during the entire study will be collected for study purposes.

All samples will be destroyed after the study.

## **7.8.3 Parameters and laboratory analyses**

### **7.8.3.1 Laboratory analyses**

All laboratory tests will be performed at the Institute of Clinical Chemistry (University Hospital Zürich) according to standard procedures.

Cytokines (IL-6) measurements will be performed with the Luminex technique at the Institute of Clinical Chemistry (University Hospital Zürich).

HMGB1 measurements will be performed by an enzyme-linked immunoabsorbant assay method.

Endotoxin Activity will be measured in EDTA whole blood using an in vitro diagnostic test (EAA™, Spectral Diagnostics Inc., Ontario, Canada). Whole blood samples will be collected from an arterial vascular access in tubes containing EDTA as anticoagulant and immediately brought to the lab at room temperature and analysed. Prior to analysis blood is thoroughly mixed by gentle inversion for 30 seconds. The test principle is the following: Specific anti-endotoxin antibodies bind to endotoxin (or lipopolysaccharide, a major cell wall constituent of

gram negative bacteria) in the blood specimen thereby forming an endotoxin-antibody complex. The opsonisation of this immune complex by complement factors primes neutrophils in the blood sample to enhance their respiratory burst in response to zymosan.

The oxidants released by the neutrophils react with luminol contained in the reaction mixture and emit chemiluminescence that can be measured using a luminometer.

The measurement is done using 3 tubes: a negative control without addition of the specific anti-endotoxin antibody, the tube where the endotoxin activity in the patient's sample is measured and a positive control after maximum stimulation of respiratory burst by an addition of an excess of exogenous endotoxin. The result of the test is given as the ratio of the endotoxin activity in the patient's sample measured by chemoluminescence and the maximum chemiluminescence of the positive control, after correction of both measurements for the basal luminescence reflecting the non-specific oxidative burst of the patient's neutrophils. Measurement results are accepted if the coefficient of variation is less than 30% for results below 0.2, and less than 15% for results equal or higher than 0.2. Otherwise the analysis is repeated. Results less than 0.4 indicate a low endotoxin activity level, those between 0.4 and 0.59 an intermediate, and those equal or higher than 0.6 a high endotoxin activity level.

### 7.8.3.2 Evaluated parameters

- Inotropic score: (dobutamine dose x1) + (adrenaline dose x 100) + (noradrenalin x 100), where all doses are expressed as µg/kg/min
- Vasopressor dependency index: Inotropic score / MAP (mmHg) x10
- Volume requirements
- Ventilation parameters
- Urine output (ml/d)
- SOFA score calculation
- SAPS score
- EAA measurement
- IL-6 and HMGB1 measurements
- Lactate, CRP and procalcitonin measurements, pH

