### **7.4 Study population**

#### **7.4.1 Inclusion Criteria**

The following inclusion criteria should be fulfilled at the time of enrollment within 24h of suspected septic shock.

Patients with septic shock, defined as: persistent catecholamine dependency with a vasopressor index > 3 after fluid resuscitation with at least 30ml/kg of i.v. fluid administered

prior to time of randomization, and at least ONE of the following criteria: metabolic acidosis, neurologic dysfunction (GCS  $\leq 14$ ), renal dysfunction, (RIFLE Class Injury or Failure), or hepatic dysfunction (Transaminases  $\geq$  twice upper limit of normal).

- Male and Female patients  $\geq 18$  years
- Endotoxin levels  $\geq 0.6$  IU within 24h from the time of suspected septic shock. If the first Endotoxin level is  $\geq 0.4 \leq 0.6$  IU EAA, the measurement should be repeated 2-3 times within the screening period of 24 hours.

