**Table: SOFA score**

| SOFA score                                                    | 0    | 1       | 2             | 3                              | 4                             |
|---------------------------------------------------------------|------|---------|---------------|--------------------------------|-------------------------------|
| Respiration
PaO 2 /FiO 2 mmHg | >400 | ≤400    | ≤300          | ≤200                           | ≤100                          |
| Coagulation
Platelets x10  /L           | >150 | ≤150    | ≤100          | ≤50                            | ≤20                           |
| Liver
Bilirubin (µmol/l)                            | <20  | 20-32   | 33-100        | 101-203                        | >203                          |
| Cardiovascular
Hypotension (mmHg)                   | None | MAP<70  | Dop or any ≤5 | Dop >5 or Norepi≤0.1, Epi ≤0.1 | Dop >15, Norepi>0.1, Epi >0.1 |
| CNS
Glasgow coma scale                              | 15   | 13-14   | 10-12         | 6-9                            | <6                            |
| Renal
Creatinin (µmol/l)                            | <106 | 106-168 | 169-300       | 301-433                        | >434                          |

Dopamine (Dop), epinephrine (Epi), norepinephrine (Norepi) doses in µg/kg/min

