### **7.9.2 Visit 2: Treatment start**

- Randomization to either SOC treatment, or SOC with oXiris™ hemofiltration, or SOC with Toraymyxin™ hemoperfusion
- EAA measurement
- IL-6 and HMGB1 measurement
- Catheter implementation
- Hemodynamic parameters: MAP, CVP, HR, CO, ELWI, PVPI
- Catecholamine doses: Epinephrine, norepinephrine, dobutamine dose
- Volume requirement
- Ventilation parameters: SaO2, FiO2, SvO2
- Urine output (ml/d)
- SOFA score, SAPS II ScorePCT, Lactate, pH

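### The cardiovascular SOFA row uses a dopamine dose that the inotropic score, the vasopressor dependency index and the drug-specific CRF dose lists leave out

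*Protocol*

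**What the plan says.** Section 7.8.3.2 defines the inotropic score as "dobutamine dose x1) + (adrenaline dose x 100) + (noradrenalin x 100", with every dose in µg/kg/min. The next line derives the index: "Vasopressor dependency index: Inotropic score / MAP (mmHg) x10". Section 6.4 makes both secondary endpoints at T0, T24, T48 and T72, along with the SOFA score.

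The SOFA table names dopamine in three of its four non-zero cardiovascular grades. Grade 3 reads "Dop >5 or Norepi≤0.1, Epi ≤0.1" and grade 4 reads "Dop >15, Norepi>0.1, Epi >0.1". Grade 2 also names dopamine; grade 1 depends on MAP alone.

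The CRF list at Visit 2 (7.9.2) is "Catecholamine doses: Epinephrine, norepinephrine, dobutamine dose", and the same three drugs are listed for Visits 3 and 4 (7.9.3) and Visit 5 (7.9.4). The Visit 1 list (7.9.1) and the flow chart row refer to catecholamine doses without naming a drug.

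Section 7.6.1 leaves concomitant treatment to the investigator, requires it to be reported on the CRF during the ICU stay, and disallows only vasopressin and corticosteroids. Entry (7.4.1) requires "persistent catecholamine dependency with a vasopressor index > 3 after fluid resuscitation".

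**The concern.** Three secondary endpoints describe circulatory support at the same visits but use different drug lists. SOFA takes dopamine into account. The inotropic score, and the index built from it, do not. The visit lists that would supply the doses follow the score rather than SOFA.

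Two things follow if dopamine is given after entry. The score and index count that part of the support as zero, so replacing a counted drug by dopamine looks like weaning. And the cardiovascular SOFA grade may depend on a dose for which Visits 2 to 5 have no named field.

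Vasopressin is also absent from the score, but it is excluded at entry (7.4.2) and disallowed during the study (7.6.1), so it cannot distort the score in a patient treated to plan. Dopamine has no such safeguard. The trial is open (section 7) and the choice of drug is discretionary, so use need not be balanced between arms. With 10 patients analysed per group (7.7), one affected patient can move an arm summary.

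**Working it through.** **Inputs.** Formulas and SOFA cut-offs are from 7.8.3.2; the entry cut of 3 is from 7.4.1. MAP 65 mmHg and the individual doses (µg/kg/min) are illustrative assumptions, because the protocol gives no such patient data.

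**Formulas.** Score = dobutamine + 100 × adrenaline + 100 × noradrenaline. Index = score / MAP × 10.

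**1. What an index of 3 means.** At MAP 65 the score must exceed 3 × 65 / 10 = 19.5. With norepinephrine alone this is a dose above 0.195.

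**2. Full switch after entry.** Norepinephrine 0.2 gives a score of 20 and an index of 20 / 65 × 10 = 3.08. Dopamine alone gives a score of 0 and an index of 0 at any dose. The SOFA row gives grade 2 at dopamine 5, grade 3 at 10 and grade 4 at 16.

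**3. Partial replacement.** Norepinephrine 0.30 gives 30 / 65 × 10 = 4.62. If this becomes norepinephrine 0.15 plus dopamine 10, the index as written is 15 / 65 × 10 = 2.31. It is halved, with the dopamine uncounted.

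**4. Addition without replacement.** Norepinephrine 0.30 plus dopamine 10 still scores 30, with index 4.62 at the same MAP. Support is understated, but the score does not fall.

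**5. Sensitivity to a weight.** The protocol gives no dopamine weight. Two values show the range. One is 1, the weight of dobutamine. The other is 0.67, from setting the two grade 4 cut-offs level: norepinephrine 0.1 is 10 score points, and 10 / 15 = 0.67.

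| At MAP 65 | As written | Weight 0.67 | Weight 1 |
|---|---|---|---|
| Dopamine 16 alone | 0 | 10.7 / 65 × 10 = 1.64 | 16 / 65 × 10 = 2.46 |
| Norepinephrine 0.15 + dopamine 10 | 2.31 | 21.7 / 65 × 10 = 3.33 | 25 / 65 × 10 = 3.85 |
| Norepinephrine 0.30 + dopamine 10 | 4.62 | 36.7 / 65 × 10 = 5.64 | 40 / 65 × 10 = 6.15 |

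The second row crosses the entry cut of 3 under either weight. A weight introduced for the endpoint would therefore change eligibility if it were also applied at entry.

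**6. Where SOFA actually needs the dopamine dose.** A patient who enters on norepinephrine or adrenaline alone has a dose above 0.003 × MAP. That exceeds 0.1 for any MAP above about 33 (0.1 / 0.003 = 33.3), so the grade is already 4 at entry whatever the dopamine dose. The missing dose matters for SOFA mainly at later visits, once the counted drugs have come down, or where dobutamine carried the patient over the entry cut.

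**The case against.** The strongest reply is that the score and the Visit 2 to 5 lists agree on the same three drugs, which fits a deliberate choice, and that a SOFA table naming dopamine does not show that it is given at these two centres. That stands: the documents do not say that any patient receives it. But the protocol adopts the table as an endpoint definition and does not disallow the drug, so the mismatch remains.

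A second reply is that dopamine would be recorded elsewhere. This is partly right. The Visit 1 field is generic and concomitant therapy is recorded throughout, so a reader who infers that no CRF field could hold dopamine goes too far. But 7.6.1 does not ask for a dose at T24, T48 and T72, and a recorded dose would still have no term in the score.

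A reader might also infer that any patient on dopamine appears unsupported, or that dopamine-only patients are mis-scored from entry. Neither holds. A zero score arises only when every counted drug is off. If the entry index is the one in 7.8.3.2, which is an inference because the names differ slightly, a patient on dopamine alone has index 0 and is not enrolled. The problem is confined to dopamine alongside a counted drug, or substituted after entry.

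**Conclusion.** The inconsistency is real and minor. As written, the inotropic score and vasopressor dependency index understate support whenever dopamine is used, and they read replacement of a counted drug as weaning. Within one patient the distortion can be large: 3.1 to 0 on a full switch, 4.62 to 2.31 on the partial replacement shown. Across the trial its size is unknown and may be nil, because frequency of use is not stated and no figure in the protocol allows an estimate. The primary endpoint (6.3) is unaffected.

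The conclusion assumes that dopamine remains permitted, as 7.6.1 implies by not excluding it, and that Visits 2 to 5 collect only the drugs their lists name. A reader might take the SOFA cut-offs as fixing a dopamine weight of 1. They do not: equating the grade 4 cut-offs gives about 0.67, and the table was not built to set weights.

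**What to change.** Reconcile the score formula and SOFA table in 7.8.3.2 with the dose lists in 7.9.2 to 7.9.4:

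- Add dopamine to the catecholamine dose fields at Visits 2 to 5.
- Include dopamine in the endpoint inotropic score and index with a weight fixed before analysis; or keep the formula and flag visits with dopamine for a sensitivity analysis.
- Leave the entry criterion unchanged, and state whether its vasopressor index is the one defined in 7.8.3.2.

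The cost is one CRF field and one line of definition, but the change is not free of consequences. With a dopamine term, the endpoint index can differ from the entry index in patients on dopamine, and the report should say so. Timing also matters: this version is dated 16.06.2016, against a planned first patient in on 01/08/2013 and last patient out on 01/02/2017. For patients already treated, dopamine doses would have to come from source records. Where those do not give a dose at the visit, flagging is the workable option.

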**Table: SOFA score**

| SOFA score                                                    | 0    | 1       | 2             | 3                              | 4                             |
|---------------------------------------------------------------|------|---------|---------------|--------------------------------|-------------------------------|
| Respiration
PaO 2 /FiO 2 mmHg | >400 | ≤400    | ≤300          | ≤200                           | ≤100                          |
| Coagulation
Platelets x10  /L           | >150 | ≤150    | ≤100          | ≤50                            | ≤20                           |
| Liver
Bilirubin (µmol/l)                            | <20  | 20-32   | 33-100        | 101-203                        | >203                          |
| Cardiovascular
Hypotension (mmHg)                   | None | MAP<70  | Dop or any ≤5 | Dop >5 or Norepi≤0.1, Epi ≤0.1 | Dop >15, Norepi>0.1, Epi >0.1 |
| CNS
Glasgow coma scale                              | 15   | 13-14   | 10-12         | 6-9                            | <6                            |
| Renal
Creatinin (µmol/l)                            | <106 | 106-168 | 169-300       | 301-433                        | >434                          |

Dopamine (Dop), epinephrine (Epi), norepinephrine (Norepi) doses in µg/kg/min

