### **6.4 Secondary endpoints**

The secondary endpoints are the following:

- Measurement of IL-6 and HMGB1 T0 i.e. patient inclusion, at T24 hours, T48 hours, and T 72 hours after treatment initiation;
- Routine measurements of norepinephrine dose, inotropic score, and vasopressor dependency index T0, T24, T48 and T72;
- Haemodynamics: MAP, CVP, HR, CO, ELWI, PVPI T0, T24, T48 and T72
- Routine measurements of volume requirement T0, T24, T48 and T72;
- Routine measurements of ventilation parameters PO2/FiO2, SvO2 T0, T24, T48 and T72;
- Urine output (ml/d)
- Lactate, procalcitonin and pH measurements at T0, T24, T48 and T72 after treatment initiation;
- SOFA score calculation at T0, T24, T48 and T72 ;
- Incidence of renal failure, ICU length of stay
- Patient survival at D28;
- Recording of AEs/SAEs

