#### **7.4.2 Exclusion Criteria**

The presence of any one of the following exclusion criteria will lead to exclusion of the subject:

Contraindications on ethical grounds

Endotoxin levels  $< 0.6$  IU EAA Pregnancy

or breast feeding

Neutropenia (circulating neutrophils  $< 500/\mu\text{l}$ )

Immune-suppressive therapy or Steroid medication  $\geq 30\text{mg/d}$  Prednisone Equivalent

Use of Vasopressin (Pitressin)

Organ transplantation within the last 12 months Terminally

ill patients classified as “do not resuscitate” Have active

bleeding or are at increased risk for bleeding

- Have a platelets count after substitution  $> 30$  G/L
- Have an INR  $> 4$
- Substitution of more than 2 erythrocyte concentrate within 6 hours

History of sensitivity to polymyxin B or to anticoagulant (heparin) HIT or allergy to heparin

Need for extracorporeal membrane oxygenation (ECMO)

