### **7.9.3 Visit 3 (24 hours) and Visit 4 (48 hours): Treatment period**

- EAA measurement
- IL-6 and HMGB1
- PCT, Lactate, pH
- SOFA score
- Catecholamine doses: Epinephrine, norepinephrine, dobutamine dose
- Volume requirement
- Hemodynamic parameters: MAP, CVP, HR, CO, ELWI, PVPI
- Ventilation parameters: SaO2, FiO2, SvO2
- Urine output (ml/d)
- AE/SAE
- In the SOC with oXiris™ treatment and SOC with Toraymyxin™ treatment groups:
  - Date and time of initiation and termination of each treatment, anticoagulation usage
  - Documentation of achievement of the treatment period or reason for premature disconnection.
- In the SOC treatment group:
  - If renal replacement therapy has to be performed: type of RRT, type of membrane, treatment conditions, duration, and anticoagulation.

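### The SOFA table labels platelets in a unit 1,000 times too small for its cut-offs and leaves the scoring of dobutamine ambiguous: a minor correction to a secondary endpoint

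*Protocol*

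**What the plan says.** Protocol section 6.4 lists "SOFA score calculation at T0, T24, T48 and T72" among the secondary endpoints. The scoring rule is the SOFA table under section 7.8.3.2.

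- **Coagulation row.** It is headed "Platelets x10", with exponent 6 and per litre in the text as read. Counts above 150 score 0; counts at or below 150, 100, 50 and 20 score 1, 2, 3 and 4.
- **Platelets elsewhere.** The bleeding-risk item in section 7.4.2 ("Have a platelets count after substitution") and its counterpart in the synopsis use a figure of 30 in G/L, that is x10^9/L.
- **Cardiovascular row.** Score 2 names dopamine, then the word any with no drug attached, with a limit of 5. Score 3 is "Dop >5 or Norepi≤0.1, Epi ≤0.1" and score 4 is "Dop >15, Norepi>0.1, Epi >0.1". The footnote covers three agents: "Dopamine (Dop), epinephrine (Epi), norepinephrine (Norepi) doses in µg/kg/min".
- **Dobutamine elsewhere.** Sections 7.9.2 to 7.9.4 (V2 to V5) list "Catecholamine doses: Epinephrine, norepinephrine, dobutamine dose". The inotropic score in section 7.8.3.2 begins "Inotropic score: (dobutamine dose x1) + (adrenaline dose x 100) + (noradrenalin x 100".
- **Renal row.** Score 3 covers creatinine 301 to 433 µmol/l; score 4 starts above 434.

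**The concern.** The platelet label and the platelet cut-offs cannot both be right. The protocol's own use of G/L shows which one is off, without any outside source. Followed to the letter, the coagulation component could never leave 0, and up to 4 SOFA points per reading would be lost.

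The cardiovascular row has a different defect. It gives dopamine a cut-off in three columns, although the V2 to V5 lists do not name dopamine. It never names dobutamine, which those lists do name. A rater scoring a patient on dobutamine alone has to guess.

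The trial analyses 10 patients per group and is meant to supply data for designing later studies. If some raters follow the table and others silently correct it, the result is avoidable noise in a repeated clinical measure.

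**Working it through.** **Coagulation row.** Conversion: 1 G/L = 10^9/L = 1,000 x 10^6/L. The cut-offs as labelled are therefore 150, 100, 50 and 20 divided by 1,000, or 0.15, 0.10, 0.05 and 0.02 G/L. The protocol's own figure of 30 G/L equals 30 x 1,000 = 30,000 x 10^6/L, which is 30,000 / 150 = 200 times the highest cut-off.

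| Platelets (G/L) | In x10^6/L | Score as labelled | Score with cut-offs in G/L |
|---|---|---|---|
| 250 | 250,000 | 0 | 0 |
| 150 | 150,000 | 0 | 1 |
| 80 | 80,000 | 0 | 2 |
| 30 | 30,000 | 0 | 3 |
| 20 | 20,000 | 0 | 4 |
| 1 | 1,000 | 0 | 4 |

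Even 1 G/L scores 0 as labelled. The discrepancy is a factor of exactly 1,000.

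**Cardiovascular row, dobutamine as sole agent.** The score-2 cell can be read in three ways. The doses and MAP values below are illustrative.

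| Reading of the score-2 cell | 3 or 5 µg/kg/min | 6 or 10 µg/kg/min |
|---|---|---|
| Any agent at 5 or less | 2 | 1 at MAP 65, 0 at MAP 75 |
| Dobutamine not scored | 1 at MAP 65, 0 at MAP 75 | 1 at MAP 65, 0 at MAP 75 |
| Dobutamine at any dose (not confirmed by the text) | 2 | 2 |

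With norepinephrine 0.08 µg/kg/min added to dobutamine 10, all three readings give 3. Once norepinephrine or epinephrine is running, the row scores 3 or 4 and the ambiguity has no effect.

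**When this can arise.** Section 7.4.1 requires a vasopressor index above 3. I take this to be the vasopressor dependency index of section 7.8.3.2: inotropic score / MAP x 10. At an assumed MAP of 65 mmHg the inotropic score must exceed 3 x 65 / 10 = 19.5.

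- Norepinephrine alone: above 19.5 / 100 = 0.195 µg/kg/min, SOFA score 4.
- Norepinephrine with dobutamine 10: above (19.5 - 10) / 100 = 0.095 µg/kg/min, SOFA score 3 or 4.
- Dobutamine alone: above 19.5 µg/kg/min.

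The ambiguity therefore hardly touches T0. It can matter at T24, T48 and T72, after norepinephrine and epinephrine have been weaned.

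**Renal row.** A creatinine of exactly 434 µmol/l falls in neither 301 to 433 nor above 434.

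**The case against.** The strongest reply is that nobody would score this way. A rater would have to turn 80 G/L into 80,000 and then compare it with 150. The label is a visible slip, and staff whose laboratory reports in G/L would probably use the cut-offs in G/L. That stands as a limit on the practical effect; it does not make the table right. The point also rests on one superscript digit, and on a cell that may have lost a word, in a table read from PDF by a program. Both need checking in the original.

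Stronger readings are tempting, and the document does not support them:

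- **That the table scores dobutamine backwards.** This follows only if the score-2 cell means any agent at 5 or less. On another reading dobutamine is simply unscored. Dobutamine is also captured in the inotropic score and the vasopressor dependency index, both secondary endpoints at the same times.
- **That every trial patient has a coagulation score of 0.** This presumes literal scoring, which nothing in the protocol shows. The protocol gives no platelet distribution either, so no average loss of SOFA points can be stated.
- **That dopamine is not recorded.** The CRF is not shown. Section 7.9.1 asks for catecholamine doses without restriction, and section 7.6.1 has all concomitant medication reported on the CRF.
- **That a device-related fall in platelets would be missed.** Section 8.2 names thrombocytopenia among the events treated as clinical outcomes, and section 8.3 requires abnormal test findings to be recorded in every group.

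**Conclusion.** The platelet unit is wrong as written, by a factor of 1,000. It sits in the operative scoring rule for a secondary endpoint read at four times. The effect on a single reading, if the label is followed, is 1 to 4 points for any realistic count at or below 150 G/L; if staff work in G/L, it is nil.

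The score-2 cardiovascular cell is ambiguous, with an effect of at most 2 points across the readings above, and only while dobutamine runs without norepinephrine or epinephrine. The renal gap is trivial.

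This is a minor correction. The same table applies to all three arms, and the primary endpoint, endotoxin activity at 72 hours, is not affected. The conclusion assumes that the exponent in the original PDF is 6; if it proves to be 9, the platelet point falls away. The dobutamine point likewise depends on the original cell being as incomplete as it reads here.

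**What to change.** 1. Check the platelet exponent and the score-2 cardiovascular cell against the original PDF.
2. Change the platelet unit in the SOFA table to x10^9/L (G/L), matching section 7.4.2.
3. Rewrite the score-2 cell so that each drug carries its own limit and dobutamine is named, and add dobutamine to the footnote.
4. Close the renal boundary so that 434 µmol/l has a score.
5. The version reviewed is dated 16.06.2016 and first patient in was planned for 01/08/2013, so patients may already have been scored. Confirm from the source data retained under section 15 that platelets were scored in G/L, and correct only the scores that were not.

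The cost is a wording change to one table and a short data check in a trial of 30 analysed patients. No procedure, sample or visit changes.
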